### Secondary analysis

The effects of the letrozole treatment on the secondary endpoints OS and TFST are tested applying the same analysis as described for the primary endpoint. The treatment’s effects on QoL, QAPFS and Q-TWiST are analyzed in a linear regression where baseline QoL is included as a covariate and the same stratum that was included for the primary analysis, i.e. grade of cell differentiation, is included as random effect. The sample size required for achieving the primary objective (assessing survival difference) will very likely suffice for a good estimate of the treatment arm difference for these continuous QoL outcomes. QAPFS, and Q-TWiST are based upon QoL assed using EQ-5D-5L and will be reported for each arm. In addition, descriptive statistics will be shown for all listed variables, broken down by study arm. The precise development of QoL over time will be presented graphically based on both the mean/median scores as well as on the proportion of patients reaching MICD, as will be described in detail in the subsequent statistical analysis plan. Similarly, the severity of side-effects of treatment over time will be shown (Fig. 3).

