**Methods:**

In this international multicenter randomized, placebo-controlled phase III trial at clinical centers in Switzerland, Germany and Austria, we plan to include 540 patients with primary, newly diagnosed FIGO Stage II to IV and histologically confirmed low- or high-grade serous or endometrioid epithelial ovarian/fallopian tube/peritoneal cancer. Patients are randomized in a 1:1 ratio into two groups: receiving blinded study treatment (letrozole or placebo tablets). When assuming a HR of 0.7, a median PFS of 18 months in the control arm and a median PFS of 25.7 months in the treatment arm, a two-sided alpha level of 5%, 3.5 years recruitment and 1.5 years observation time, we expect 330 events to have occurred within these 5 years in the total cohort yielding a power of 90%. Follow-up data for the whole cohort will be collected for up to 10 years and for the low-grade cancer for up to 12 years.

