**Fig. 2 Fig2:**
[figure not shown]
Overview of all time-dependent endpoints. *QAPFS   *Quality-adjusted Progression Free Survival, *Q-TWiST   *Quality-adjusted Time Without Symptoms and Toxicity,* TOX*   Toxicity*, TWIST*   Time Without Symptoms and Toxicity*, REL*  Relapse*, PFS   *Progression Free Survival*, OS   *Overall Survival

Additionally, the following explorative and translational objectives are evaluated:To explore the correlation between the activity values of the wearable activity tracker (objective QoL measuring tool) and the patient reported QoL scoresTo explore the feasibility of digitally obtained biomarkers for clinical trialsTo explore the efficacy of letrozole maintenance therapy in correlation to anti-VEGF and PARPi maintenance therapy as measured by PFSTo explore the efficacy of letrozole maintenance therapy in comparison to no maintenance therapy (placebo) according to presence/absence of residual tumor tissue as measured by PFSTo explore the effect of resilience (Connor-Davidson Resilience Scale 10 score categories) on PFS and over timeTo explore the resectability in primary or interval debulking surgery in correlation to the Age Adjusted Charlson Comorbidity Index (AACCI) and the G8 fragility questionnaire scoreTo assess the safety and tolerability of the letrozole group in comparison to the placebo control group and historic breast cancer cohortTo determine molecular markers of ER + /ER- and its association with clinico-pathological parameters [35–38]To determine pathways involved in estrogen response (e.g. EIG121, ESR1/2 and PI3KCA) [39–41]To determine the mutational load of involved tumorsTo determine the predictive role of a glycomic signature in association with clinico-pathological parameters [42]To determine synergistic effects of combined maintenance therapies by state-of-the-art molecular methods [43, 44]

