### Sample size consideration and statistical analyses

#### Sample size considerations of the whole cohort

We estimated how many events are needed to achieve a 90% power to detect a hazard ratio (HR) of 0.70 between the two treatment arms (hazard letrozole/hazard placebo, assuming an exponential distribution of PFS). From the ICON7 adjuvant trial [10], which investigated bevacizumab in the adjuvant maintenance setting, it is expected that PFS is approximately exponentially distributed and the median PFS under standard care is 18 months. The assumed HR of 0.70 would increase the median PFS in the treatment arm to 25.7 months.

Calculations were done assuming a two-sided alpha level of 5% and a log-rank test for comparison. The approximation described by Machin et al., (2009) resulted in a required sample size of 330 events, i.e., cases with progression over both study arms [45]. The recruitment will continue until this number of events is observed and the power of 90% has been achieved. When assuming, in addition to the aforementioned conditions, a uniform recruitment rate during three and a half years and a dropout rate of 10%, a total number of 540 patients would suffice to achieve the target number of 330 events five years after study start (calculated using the method by Lachin & Foulkes, 1986) [46].

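### QAPFS and Q-TWiST are durations subject to censoring, but the plan analyses them by a linear regression with no allowance for censoring and no time horizon

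*Protocol article*

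**What the plan says.** In the protocol article, Secondary analysis, the treatment's "effects on QoL, QAPFS and Q-TWiST are analyzed in a linear regression where baseline QoL is included as a covariate"; in the same model "grade of cell differentiation, is included as random effect". The paragraph adds that the sample size "will very likely suffice for a good estimate of the treatment arm difference for these continuous QoL outcomes", so it treats all three as complete continuous measurements. On how they are built it says only that "QAPFS, and Q-TWiST are based upon QoL assed using EQ-5D-5L and will be reported for each arm".

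The legend of Fig. 2 puts QAPFS and Q-TWiST, together with PFS, OS and the toxicity and relapse periods, under the title "Overview of all time-dependent endpoints". The opening sentence of Secondary analysis sends OS and TFST to the same Cox analysis as the primary endpoint.

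The only restricted-mean horizon in the article is the 5-year one under Primary analysis. It applies to PFS, and only if hazards look non-proportional. On timing, the abstract expects, with "3.5 years recruitment and 1.5 years observation time, we expect 330 events to have occurred within these 5 years". Blinding procedures puts the final PFS analysis at least 1.5 years after the last inclusion.

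**The concern.** A regression with baseline QoL as covariate needs one outcome value per patient. A woman alive and progression-free at the data cut has no complete QAPFS, and a woman still alive has no complete Q-TWiST. Unless something is done about this, the value accumulated so far is analysed as if it were final.

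If letrozole works, more letrozole patients are in that position, and their longer durations are cut more. The estimated difference is then pulled toward zero and depends on how fast patients were recruited. The trial's hypothesis is longer PFS without loss of QoL, and these two endpoints combine both sides. A method that shortens the survival side can misstate that trade-off.

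**Working it through.** **Inputs** (Sample size considerations of the whole cohort; Blinding procedures): exponential PFS, medians 18 and 25.7 months, HR 0.70, two-sided alpha 5%, power 90%, 540 patients randomized 1:1, uniform accrual over 42 months, 18 months of further follow-up, 10% dropout. Administrative censoring is therefore uniform on 18 to 60 months. The article does not say how the 10% accrues. I assume an exponential rate reaching 10% by month 60, and show results with and without it.

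**The plan's own figure.** Events = 4(1.960 + 1.282)²/(ln 0.70)² = 330.4, so the stated 330 is reproduced. With 540 × 0.9 = 486 patients, about 336 events are expected at 5 years, which also agrees.

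**Hazards.** Control: ln 2/18 = 0.03851 per month. Letrozole: 0.70 × 0.03851 = 0.02696 per month (median 18/0.70 = 25.7).

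**Censored for PFS at the 5-year cut, no dropout:** (e^(−18λ) − e^(−60λ))/(42λ).
- Control: (0.500 − 0.099)/1.617 = 0.248
- Letrozole: (0.616 − 0.198)/1.132 = 0.368

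With dropout these become 0.267 and 0.386.

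**Mean observed PFS time, censored times entered as they stand:** (1 − proportion censored)/λ.
- Control: 0.752/0.03851 = 19.53 months
- Letrozole: 0.632/0.02696 = 23.43 months
- Difference: 3.90 months (3.73 with dropout: 22.76 − 19.03)

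A simulation of 3,000 trials with dropout gave 3.74.

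**Restricted mean PFS difference:** each arm's mean is (1 − e^(−λτ))/λ. At 60 months it is 29.74 − 23.39 = 6.34. At 48 months it is 26.93 − 21.88 = 5.05. Unrestricted, it is 37.10 − 25.97 = 11.13.

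| Target | True difference (months) | Shortfall of the observed-time difference (no dropout, dropout) |
|---|---|---|
| Unrestricted mean | 11.13 | 65%, 67% |
| 60 months | 6.34 | 39%, 41% |
| 54 months | 5.72 | 32%, 35% |
| 48 months | 5.05 | 23%, 26% |
| 42 months | 4.32 | 10%, 14% |
| 36 months | 3.56 | none |

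If observed times are also capped at 48 months, the differences are 3.71 and 3.55, so the 4-year shortfall is 27% and 30%. The absence of a shortfall at 36 months does not make the method valid. Without dropout, the observed-time difference is the restricted-mean difference averaged over horizons from 18 to 60 months, so it answers to the accrual pattern and not to any chosen horizon.

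**From PFS time to QAPFS.** A utility that is constant and equal in both arms multiplies both columns and leaves the percentages unchanged. At an assumed utility of 0.80, the 5-year comparison is 3.0-3.1 versus 5.1 months.

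**Other handling and timing.**
- Patients with an event only: 16.61 − 14.91 = 1.70 months, 73% below the 5-year value.
- Cut at 5 years 3 months with accrual still 42 months: 4.26 months (4.06 with dropout), 33-36% below.
- Data 10 years after study start, times capped at 60 months: 6.34 months without dropout (no shortfall) and 5.99 with it (about 6%). Uncapped without dropout, 9.06 months is 19% below the unrestricted 11.13.

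**Q-TWiST.** This would need toxicity time, survival after relapse and utilities. The article gives none of these, and no OS planning assumption for the whole cohort, so no figure is derived.

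**The case against.** The strongest defence is that the article does not say how the per-patient value is formed. A linear regression can be run on censoring-weighted or pseudo-value outcomes, and such detail is commonly left to an analysis plan, which is not shown. This has some force. But what the paragraph expressly leaves to that plan is the presentation of QoL over time and of the proportions reaching an important difference. The regression itself is stated as the chosen analysis, on outcomes called continuous, beside a Cox model for the other two durations. Followed as written, it takes no account of censoring, and the random effect for grade does not change that.

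Four stronger readings are tempting, and the document does not support them:

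- **A fixed loss of about 40%.** This figure needs censored times entered as observed, a 5-year target, equal constant utility and analysis at the PFS cut. The article sets none of these for QAPFS. The 5-year target is also barely estimable at that cut, because only the earliest entrants reach 60 months.
- **The same percentage for Q-TWiST.** Nothing in the article allows that calculation.
- **A utility loss on letrozole counted almost in full while the benefit shrinks.** With an assumed loss of 0.10, the full 5-year cost is 0.10 × 29.74 = 2.97 months, and on observed time it is 0.10 × 22.76 to 23.43 = 2.28 to 2.34. So 21-23% of the loss is cut as well.
- **A threat to the main conclusion.** PFS, OS and TFST are analysed by Cox models, which handle censoring. With no true arm difference and independent censoring, both arms are truncated alike and no false benefit arises.

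**Conclusion.** The concern holds in a limited form. The stated analysis of QAPFS and Q-TWiST fits neither the nature of the endpoints nor the planned follow-up. It has no censoring method and no horizon, and under the planning assumptions it pulls the QAPFS difference toward zero. The understatement is about 39-41% against a 5-year restricted mean and about 23-30% against a 4-year one. It rests on exponential PFS at the planned medians, a cut 5 years after study start, censored times used as observed, and equal constant utility. It is smaller for shorter horizons or longer follow-up, and larger if only patients with events are used. For Q-TWiST the defect is the same in kind, with its size unknown. Since these are two secondary endpoints and the primary analysis is sound on this point, this should be fixed but does not put the trial's main result at risk.

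**What to change.** Before unblinding, so that the horizon cannot be chosen on the results:

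1. Name one horizon within follow-up for both endpoints, for example 4 years if they are analysed at the 5-year cut, and state when they are analysed.
2. Replace the linear regression for these two endpoints. Estimate restricted mean state times from Kaplan-Meier curves up to that horizon (PFS for QAPFS; TOX, TWiST and REL for Q-TWiST), weight them by EQ-5D-5L utilities, and report the arm difference with a bootstrap interval resampled within grade.
3. If adjustment for baseline QoL is to be kept, use inverse-probability-of-censoring-weighted regression to the same horizon.
4. Keep the linear models for the QoL scores.

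Simply moving these endpoints to the Cox model used for OS and TFST would not do. Once time is weighted by utility, the censored amount is related to the outcome itself, and estimating each state's duration before weighting avoids this.

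The cost is protocol or SAP wording and modest programming, with no new data.

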**Fig. 3 Fig3:**
[figure not shown]
Envisioned results on a feeling and energy scale during maintenance phase, after at least 4 cycles of chemotherapy and potential surgery, determined via questionnaires and objectified via activity tracker. *EQ-5D*   European Quality of Life Scale*, *5-Dimensions*, FACT-ES*   Functional Assessment of Cancer Therapy—Endocrine subscale*, FACT-0*   Functional Assessment of Cancer Therapy – Ovarian cancer symptoms subscale*, PFS*   Progression Free Survival

### Interim analysis

No interim analysis is planned for the primary analysis on the full set of patients (HGOC + LGOC). However, since the LGOC study recruitment continues after closure of the study for the whole cohort, the subgroup analysis of the LGOC should be regarded as an interim analysis by an O`Brien-Fleming group sequential design for this cohort. The boundaries for the group sequential design at the interim look will be based on the actual number of observed events and will be calculated using the alpha-spending function for an O’Brien-Fleming design. The final analysis will be performed after observation of 121 events.

### Subgroup analysis

We will explore the impact of the experimental treatment vs the control in the following subgroups:- Bevacizumab treatment.- PARP inhibitor treatment.- Residual disease.- Grade (LGOC/HGOC).- Weak and strong ER expression.- Resilience categories/scores.- The elderly population (≥ 75 years).

For each subgroup, the primary analysis will be repeated. No other subgroups or subgroup analyses are pre-specified.

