## Abstract

**Background:**

A high percentage of epithelial ovarian cancers (EOC) express the estrogen receptor (ER), which is an ideal target for endocrine therapy. Letrozole is a proven, potent aromatase inhibitor, extensively tested and used in the treatment of ER positive breast cancer. In addition, it seems a potent drug for patients with heavily pre-treated OC as demonstrated in several distinctive settings. However, it has never been evaluated prospectively in a maintenance setting for ovarian cancer after standard of care. The here proposed trial aims to define a population of EOC patients, who would benefit from the effectiveness of the generic agent letrozole, with little expected toxicity and thus beneficial impact on overall quality of life (QoL).

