Several small series suggested a benefit in low-grade serous ovarian cancer (LGOC) patients, suggesting that there are subgroups of patients with a specific tumor biology that respond very well to endocrine therapy [25, 26]. LGOC is a rare histological subtype and biologically distinct from HGOC. Only approximately 5–10% of all ovarian cancers are of low-grade serous type. Gershenson et al*.* [17, 18]*,* presented retrospective analyses of endocrine maintenance therapy (with diverse regimens, including anastrozole, letrozole and tamoxifen) for LGOC. For patients receiving endocrine maintenance therapy (*n* = 70) after platinum-based adjuvant chemotherapy, PFS significantly improved as compared to patients under observation only (*n* = 133, 64.9 months; 95% CI 43.5 to 86.3; versus 26.4 months; 95% CI 21.8 to 31.0, *p* < 0.001) [17]. Most patients received treatment with letrozole (54%) or tamoxifen (28%) [13]. In 2012, the same authors described already a high clinical benefit rate in a retrospective analysis obtained from medical records ranging from 1989 until 2009 covering 64 patients with recurrent LGOC [18]. In spite of the known limitation of retrospective analyzed data as a long study period, incomplete data, potential referral bias, heterogeneous therapies, and varying follow-up practice patterns, patients receiving different regimens of endocrine maintenance therapy for relapse showed a response rate of 9% and stable disease of 62% [18]. This is of major significance as—similar to ER-positive breast cancer patients – LGOC affects mostly younger women with a rather poor prognosis [17].

The rationale for exploring endocrine therapy for the treatment of ovarian cancer patients is based on the high ER/PR expression as a predictive marker, since ovarian cancer is partly driven by the estrogen-pathway [27].

In spite of these clear distinctions between HGOC and LGOC, primary treatment strategies in both diseases have so far been similar, i.e. maximal surgical cytoreduction, followed by adjuvant chemotherapy with carboplatin and paclitaxel. None of the studies and analyses on endocrine treatment of ovarian cancer so far were prospective, in the maintenance setting, and potentially in combination with other maintenance treatments, but rather as a stand-alone treatment regimen in heavily pre-treated patients. Of note, generally no information in regards to ER/PR expression was provided.

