### Aims

There is a need to evaluate endocrine therapy in a prospective large phase III trial including and focusing on QoL aspects. We present a phase III randomized double-blind placebo-controlled multi-center trial that will assess the effect of the aromatase inhibitor letrozole as maintenance therapy in patients with FIGO Stage II-IV low and high-grade ovarian cancer of endometrioid or serous histotype. This experimental arm will be compared to the current standard, namely use of no maintenance endocrine therapy after the end of adjuvant chemotherapy, whereas, combined treatment with the new approved treatment options in this phase is allowed and has been proven safe [32, 33].

Based on the evidence presented above, we hypothesize that the letrozole maintenance arm will lead to a prolongation of PFS in these patients with no decrease of QoL. PFS has been selected based on previous data from our own study [28] and a recent meta-analysis [34] demonstrating a high potential benefit in regards to prolongation of the time to first relapse by 8 months using endocrine treatment in the maintenance setting.

Moreover, this study aims to identify the population that would benefit the most from this endocrine therapy in respect to prolonged quality of life (QoL). QoL will be assessed, prior, during, and after the intervention period, by both validated QoL questionnaires as well as by activity measurements. In addition, the survival status will be evaluated in relation to fragility and vulnerability as well. To this end, the G8 score will be used to assess fragility by patients over 75 years of age and the CD-RISC-10 score to assess resilience in the whole cohort.

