### Inclusion criteria

Patients must be ≥ 18 years of ageWilling and able to attend the visits and to understand all study-related proceduresPrimary, newly diagnosed FIGO Stage II to IV and histologically confirmed low or high grade serous or endometrioid epithelial ovarian/fallopian tube/peritoneal cancer(Interval-) debulking performedEastern Cooperative Oncology Group (ECOG)-Performance Status 0–2Signed informed consents (ICF-1; ICF-2)Paraffin-embedded tissue or paraffin-embedded cell block (from ascites) availablePositivity (≥ 1%) for ER expression (as determined by the central Histopathology Core Facility of the MATAO trial)At least 4 cycles of platinum-based chemotherapy (neoadjuvant allowed)Negative serum pregnancy test in women of childbearing potential (women of childbearing potential defined as: premenopausal or less than 12 months of postmenopausal amenorrhea, and who have not undergone surgical or radiation sterilization)

Note: Patients under concurrent maintenance treatment with Bevacizumab and/or PARP Inhibitors are eligible

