## Discussion

Despite optimized treatment for epithelial ovarian cancer the prognosis is poor with a maximum reported 5-year overall survival rate of up to 50% [1]. At present, the standard of care after a maximal surgical cytoreduction effort followed by adjuvant chemotherapy with carboplatin/paclitaxel is limited with maintenance therapy with bevacizumab for FIGO stages III-IV and additionally PARP inhibitor for HGOC with a BRCA mutation and partial or complete response to carboplatin/paclitaxel. Therefore, additional treatment options, particularly maintenance therapy regimens that might prolong this period of response are needed [48]. Nevertheless, some patients might be cured from the disease by the primary treatment already, so it is important that this treatment should be as tolerable as possible. A high percentage of epithelial ovarian cancer expresses ER, which is an ideal predictive marker for endocrine therapy response [49].

Letrozole is a potent aromatase inhibitor extensively tested and used in ER positive breast cancer patients and has also been tested in several smaller series for patients with heavily pre-treated epithelial ovarian cancer [29]. Letrozole in general is well tolerated and has been commonly used in breast cancer patients for more than 20 years. It has a preferable toxicity profile. Approximately 30% of patients have some mild symptoms like arthralgia, vaginal dryness and hot flushes. Recently, the combined use of Letrozole and Bevacizumab and Olaparib, respectively, has proven to be safe, as all toxicity observed was attributed solely to the new compounds and not to the letrozole [32, 33].

So far, it has not been prospectively evaluated in the adjuvant maintenance setting for ovarian cancer primary treatment. The MATAO trial aims to fill this gap and will evaluate for the first time prospectively the benefit of letrozole versus placebo in the maintenance setting of ER positive ovarian cancer.

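### The letrozole effect by ER level is pre-specified only as a weak-versus-strong split, which loses a quarter to a half of the information if benefit changes gradually with ER

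*Protocol article*

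**What the plan says.** The Subgroup analysis section of the protocol article lists seven subgroups, one of which is "Weak and strong ER expression". The method for all of them is one sentence: "For each subgroup, the primary analysis will be repeated". The section ends with "No other subgroups or subgroup analyses are pre-specified". No definition of weak or strong is given. In the same list, resilience may be analysed as categories or as scores; ER has no such alternative.

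ER has a special standing elsewhere in the article:

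- The abstract says that many of these cancers "express the estrogen receptor (ER), which is an ideal target for endocrine therapy".
- The Rationale section says that the case for endocrine therapy is "based on the high ER/PR expression as a predictive marker".
- The Discussion says that the tumour often "expresses ER, which is an ideal predictive marker for endocrine therapy response".
- Eligibility requires at least 1% positivity "for ER expression (as determined by the central Histopathology Core Facility of the MATAO trial".

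The abstract also gives as a purpose of the trial to define the patients who would benefit from letrozole. The Aims section says that "this study aims to identify the population that would benefit the most from this endocrine therapy", although that sentence goes on to tie the benefit to quality of life.

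**The concern.** ER level is the article's own leading candidate for explaining who benefits. If the effect of letrozole on PFS grows steadily with ER expression, splitting patients into two classes treats all tumours within a class as alike and uses only the difference between two averages. That estimates a gradient less precisely than a model using the graded value, and it cannot show where along the ER range benefit becomes visible.

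This is not merely a detail left open for the analysis plan. The two-class form is stated and the list is closed, so an analysis plan that only supplied the cut would keep the loss. A graded ER model added after unblinding would be post hoc. The explorative and translational objectives do not fill the gap: they cover molecular markers of ER-positive and ER-negative disease and estrogen-response pathways, not the treatment effect on PFS across ER level.

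**Working it through.** **Inputs from the protocol article** (Sample size considerations of the whole cohort; Randomization): HR 0.70, two-sided 5%, 90% power, 330 events, 540 patients, control median 18 months, exponential PFS, uniform accrual over 3.5 years, analysis at 5 years, 10% dropout, 1:1 allocation.

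**Inputs assumed:** the distribution of ER (normal or uniform on its scale), the share of patients in each class, and a log hazard ratio that is linear in ER. The article gives none of these.

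**Step 1: the plan's own figures.**
- Events: 4 × (1.960 + 1.282)² / (ln 0.70)² = 330.4, which agrees with 330.
- Patients: averaged over the arms, the event probability by month 60 without dropout is 0.692. Then 330 / 0.692 = 477, and 477 / 0.90 = 530, within 2% of 540.

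**Step 2: information kept by a two-class split.** For a linear effect this is the squared correlation between the marker and its class indicator. With a share q in one class, it is φ(c)² / [q(1 − q)] for a normal marker, where c is the normal quantile at the cut, and 3q(1 − q) for a uniform marker. For example, at 50:50 the normal case gives 0.3989² / 0.25 = 0.637 and the uniform case 3 × 0.25 = 0.75.

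| Split | Kept, normal | Kept, uniform | 330 events act like (normal / uniform) |
|---|---|---|---|
| 50:50 | 64% | 75% | 210 / 248 |
| 30:70 | 58% | 63% | 190 / 208 |
| 20:80 | 49% | 48% | 162 / 158 |
| 10:90 | 34% | 27% | 113 / 89 |

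**Step 3: power for the interaction.** Power = Φ(b × √(330 × 0.25 × kept) − 1.96), with b the change in log hazard ratio per standard deviation of ER. The slope that gives 80% power with the graded marker is b = (1.960 + 0.842) / √82.5 = 0.308. With that slope the weak/strong contrast has:
- 50:50, normal: Φ(2.80 × √0.637 − 1.96) = Φ(0.28) = 61%
- 50:50, uniform: Φ(2.80 × √0.75 − 1.96) = Φ(0.47) = 68%
- 20:80, normal: Φ(2.80 × √0.49 − 1.96) = Φ(0.00) = 50%

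**Step 4: check by simulation.** 1,500 trials of 540 patients were run per setting, with dropout of 10% over five years (about 363 events), no prognostic effect of ER and no grade strata. A Wald test of the treatment-by-ER term was used.

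| Setting | Graded ER | Weak/strong |
|---|---|---|
| Linear effect, normal, 50:50 | 82% | 62% |
| Linear effect, uniform, 50:50 | 83% | 70% |
| Linear effect, normal, 20:80 | 82% | 49% |
| Linear effect, uniform, 20:80 | 81% | 45% |
| Step exactly at the cut, normal, 50:50 | 64% | 83% |

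With no interaction both tests rejected in about 5% of trials. At 20:80 the simulated information ratio was 42% to 43%, a little below the closed form. The last row shows that the ranking depends on the shape of the effect.

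**The case against.** Several points on the other side stand in full or in part.

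- **The scale is not stated.** A reader might infer that a percentage is stored for each patient and that weak/strong is a cut of it. The Inclusion criteria give only a central positivity rule at 1%. Weak and strong could describe staining intensity or a composite score. The figures above therefore describe a generic graded marker, not a known split.
- **The size is conditional.** Distribution, cut and effect shape are all assumed. A reader might conclude that two classes are always the worst choice; the step scenario shows that they are not. The article, however, gives neither a cut nor a reason to expect a step.
- **The analysis is exploratory.** The section says it will explore these subgroups, no alpha or power is attached to ER, and the primary PFS comparison and its 330 events are untouched. This limits the weight of the point but does not remove it.
- **The analysis plan could add a model.** Detail of this kind is often placed there, and the closing sentence does not forbid a supplementary analysis. Still, the article states the coarser form as the complete pre-specified set.
- **The power comparison is between two interaction tests,** and the article specifies neither. It is a fair measure of what a contrast between two class-specific hazard ratios can show, but it is not the power of a test the article plans.
- **The 1% limit.** A reader might expect a continuous model to validate the entry threshold. It cannot, because nobody below 1% is randomised, and precision near 1% will be poor if few patients lie there.

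**Conclusion.** The point holds as a worthwhile improvement to an exploratory analysis, not as a flaw in the trial's main result. The article names ER as a predictive marker, wants to find who benefits, and pre-specifies only a two-class analysis of the letrozole effect by ER.

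If benefit is graded, the split keeps at most about 64% to 75% of the interaction information for a normal or uniform marker, and about half at 20:80. In power terms, 80% falls to about 61% to 68% at an even split and to about 50% at 20:80. These figures rest on an assumed ER distribution, cut and linear log hazard ratio, and they reverse for a true step at the cut. The documents do not support a claim that a known percentage is being discarded, or that the loss has one fixed size.

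**What to change.** Keep weak/strong for display and write down its definition (scale and cut) in advance. Before unblinding for the whole-cohort PFS analysis, pre-specify one further exploratory analysis in the Subgroup analysis section or the analysis plan:

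- a Cox model for PFS, stratified by grade as in the primary analysis, with treatment, the centrally determined ER value on its recorded scale (percentage or score), and their interaction;
- ER entered linearly and, to allow for a threshold or plateau, as a restricted cubic spline;
- a plot of the hazard ratio with its 95% confidence interval against ER level, with a note that it does not extend below the 1% entry limit.

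The cost is a paragraph of text, a few lines of code and one more exploratory model to report and interpret cautiously. No extra patients are needed, and no new assay if the central laboratory's graded result has been kept. The trial team should confirm now that it is.
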